#### Secondary endpoints

To explore the mechanisms underlying the Lactobreath profiles, first, unsupervised, integrative analysis (such as correlation-based tools like regularised canonical correlation analysis) will be used to link the metabolic traits (ie, urinary metabolome, lactose-derived colonic gases) and clinical traits with specific features of the Lactobreath profiles. In the second step, integrative data analysis tools, such as similarity network fusion tool, and Data Integration Analysis for Biomarker discovery using Latent variable approaches for ‘Omics’ (DIABLO; MixOmics)^102 103^ will be used to combine breath markers and pairs of metabolic/continuous clinical traits with respect to categorical clinical traits to explore the potential of these traits for improving the predictivity of the Lactobreath markers.

Statistical analyses will be conducted using R and Python programming environments. The final trial report will describe and justify any deviation from the original statistical plan. The stopping rules for the study are a single serious adverse event.

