## Hypothesis and objectives

### Hypothesis

We hypothesise that lactose consumption generates different breath metabolomic profiles in people with lactose tolerance and those diagnosed with LI. These breath profiles are also expected to be associated with GI symptoms of LM.

The primary objective of the study is to identify postprandial metabolic profiles in human exhaled breath associated with GI symptoms of LM (Lactobreath profiles).

Secondary objectives:

To identify postprandial metabolic profiles in human exhaled breath reporting on the clinical traits associated with LM (Lactobreath profiles), including:▪ Genetic polymorphisms regulating the expression of the lactase gene.▪ Breath hydrogen.▪ Lactose-derived urinary metabolites.To mechanistically link Lactobreath profiles with metabolic traits associated with LM, including▪ Colonic gases measured by the Atmo Gas Capsule.▪ Urine metabolome.▪ Gut microbiota composition.To associate colonic gases and symptoms of LI with bowel sounds using a digital biosensor.

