### Statistical analysis

#### Primary endpoint

Supervised machine learning algorithms (such as random forest and partial least squares discriminant analysis) will be applied based on Zheng *et al*^100^ and will identify molecular breath profiles that discriminate different clinical traits associated with LM based on the levels of metabolites in the exhaled breath after the intake of lactose. Models will be created to explore separately the breath profiles that are discriminated for each trait of LM, including the response to the LHBT, polymorphisms for LP, lactose-derived metabolites in urine and the GI symptoms of LI taken individually and collectively. To reduce overfitting and deliver reliable estimates of the models, we will apply machine learning with voting, a strategy for classification based on selecting the output with the most classes. Clinical traits will be modelled as either categorical variables, continuous variables or both, where appropriate. This analysis will be conducted first on a subset of 50% of the recruited participants to allow the most predictive metabolites to be identified within the timeframe of the study. The subset will be balanced to represent the three test groups. The same analysis workflow will later be applied to the whole cohort, with 20 participants (stratified for group) removed from all modelling to allow for internal validation of the models. The best profiles (Lactobreath profiles) that associate the breath exhalome with each of the clinical traits of LM will be tested in the 20 remaining participants to assess their validity. Further, to consider the specificity of the Lactobreath profiles for lactose metabolism, the profiles will be evaluated in the participants assigned to the glucose test with additional comparisons between intervention types (glucose vs lactose) across all three participant groups. The molecular profiles with the best performance for predicting LM clinical traits will be retained to determine the identity and quantification of the molecules composing the selected profiles.

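### Breath features selected on the clinical traits are then correlated with those same traits, so the clinical-trait links carry no evidence unless selection is accounted for

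*Protocol article*

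**What the plan says.** Under Statistical analysis, Primary endpoint, the Protocol article applies supervised algorithms (random forest and partial least squares discriminant analysis are the examples) that "will identify molecular breath profiles that discriminate different clinical traits associated with LM based on the levels of metabolites in the exhaled breath". The traits are listed as "including the response to the LHBT, polymorphisms for LP, lactose-derived metabolites in urine and the GI symptoms of LI taken individually and collectively". Selection continues after modelling: "The molecular profiles with the best performance for predicting LM clinical traits will be retained". Twenty participants, stratified by group, are kept out of all modelling, and the best profiles are tested in them.

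Under Statistical analysis, Secondary endpoints, the first step is described as "unsupervised, integrative analysis (such as correlation-based tools like regularised canonical correlation analysis". It "will be used to link the metabolic traits (ie, urinary metabolome, lactose-derived colonic gases) and clinical traits with specific features of the Lactobreath profiles". After that, similarity network fusion and DIABLO "will be used to combine breath markers and pairs of metabolic/continuous clinical traits with respect to categorical clinical traits". The participants used for either step are not named.

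The corresponding objective, under Hypothesis and objectives, is "To mechanistically link Lactobreath profiles with metabolic traits associated with LM". The traits named there are colonic gases, the urine metabolome and the gut microbiota.

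**The concern.** The features entering the linking step are those of "The best profiles (Lactobreath profiles) that associate the breath exhalome with each of the clinical traits of LM". They are in the profile because they track a clinical trait. Correlating them with that trait again, in the people used to choose them, asks whether features chosen for correlating do correlate. The answer is yes even if every feature is noise. Canonical correlation is itself an unsupervised method, but that does not remove the dependence, because the trait labels chose its input.

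At stake is the interpretation of the secondary results. Correlations produced by selection could be reported as links between breath and clinical traits. Some of this can also pass to metabolic traits that share information with a selecting trait. The lactose-derived urinary metabolites are selecting traits and are measured in the same urine samples as the urine metabolome. Colonic hydrogen may correlate with the breath-hydrogen response.

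**Working it through.** The article gives no figure for this step, so there is none to reproduce.

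**Inputs from the Protocol article**
- Lactose arm 100, hold-out 20. Modelling set n = 100 − 20 = 80, assuming the hold-out comes from the lactose arm.
- Two-sided α = 0.05 with false discovery rate correction (stated under Primary endpoint; the family is not given).
- Candidate features: thousands were detected in the pilot study (Statistical power calculation).

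**Assumptions**
- p = 2,000 features, k = 20 selected, a 40:60 binary trait, independent features, and univariate ranking in place of random forest or PLS-DA.

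**1. Selected features against the selecting trait, no true association**
- Keeping 20 of 2,000 keeps the top 1% by |r|. Under the null, r√n is roughly standard normal, so the cut-off is |z| = 2.576.
- Mean |z| beyond the cut-off = φ(2.576)/0.005 = 2.89, so mean |r| ≈ 2.89/√80 = 0.32.
- The smallest selected |r| ≈ 2.576/√80 = 0.29. The critical |r| at n = 80 is 0.22, so every selected feature is nominally significant with p of about 0.01 or less. All 20 also pass a Benjamini–Hochberg correction applied only within the profile, where the largest p-value is compared with 0.05.
- Score of the 20 sign-aligned features: k·r/√(k + k(k−1)r²) = 20 × 0.32/√(20 + 380 × 0.1024) = 6.4/7.68 = 0.83.
- Simulation agrees: mean |r| 0.32, score r 0.83, and about 0 in 20 held-out people.

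**2. Sensitivity (simulation, null)**

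| Setting | Score r with selecting trait |
|---|---|
| p = 265 to 3,000, k = 10 to 20, n = 80 | 0.66 to 0.84 |
| n = 100, p = 1,000, k = 20 | 0.78 |
| Features correlated through 10 latent factors | 0.59 |
| Hold-out pooled back in (p and k as in row 1) | 0.55 to 0.72 |
| Hold-out of 20 only | about 0 |

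The share of selected features passing within-profile correction depends on how strict the selection is: from 0.22 (p = 265, k = 20) to 1.00 (p of 1,000 or more).

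**3. The named method**

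Regularised canonical correlation of 20 selected features with 6 clinical traits (n = 80, p = 1,000, null, 60 runs) gave a first canonical correlation of 0.83, against 0.67 for 20 random features (ridge 0.1). A permutation test run after selection rejected in 100% of runs. Repeating the selection inside each permutation brought this to 5% (ridge 0.1) and 2% (ridge 0.5).

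**4. Metabolic traits with no breath link**
- Suppose the trait correlates 0.5 with the scale underlying the 40:60 clinical trait. Its correlation with the binary trait is 0.5 × φ(0.253)/√(0.4 × 0.6) = 0.5 × 0.386/0.490 = 0.394.
- Expected r with the score: 0.394 × 0.83 = 0.33, above the critical 0.22. Expected r with one feature: 0.394 × 0.32 = 0.13, below it.
- Spread ≈ √(1 − 0.394²)/√79 = 0.103. Chance of exceeding 0.22: Φ((0.327 − 0.22)/0.103) = 0.85 for the score and Φ((0.126 − 0.22)/0.103) = 0.18 per feature.
- Simulations gave 85 to 90% for the score and 18 to 19% per feature. Over other choices of p, k and trait type the per-feature range was 15 to 31%.
- With zero correlation, the rate was about 5% for both.

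**5. Gain from adding a trait to the markers (simplified, two predictors)**
- The metabolic trait alone explains R² = 0.394² = 0.16.
- Added to the over-fitted score: (0.394 − 0.83 × 0.327)²/(1 − 0.327²) = 0.0150/0.893 = 0.02. Simulation gave 0.02 against 0.16 to 0.17 alone. The in-sample comparison hides the gain.

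**The case against.** Five points can be made for the plan.

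- **The hold-out.** Profiles are tested in 20 people outside the modelling and also evaluated in the glucose arm, so a pure-noise profile would probably be exposed: under the null its score reached p < 0.05 in the right direction in the hold-out in only 2 to 3% of runs. This stands as a check that a profile predicts a trait. It does not correct the size of links estimated elsewhere, and the linking step is not made conditional on it.
- **Who is analysed is not stated.** Use of the selection set is an inference, although it is the plain reading in a single-cohort study. Resampling detail may sit in the full protocol. But the article does state both the input (profile features) and the targets (including the selecting traits), and those two create the problem.
- **No test is specified.** The secondary section names none, and false discovery rate control over all measured features gives any false hit in only 3 to 7% of null runs. That protects tests over the full family. It does not correct the inflated correlations of the selected features.
- **The mechanistic objective.** A reader might infer that this objective is met by construction. The documents do not support that. It concerns metabolic traits, most of which are not selecting traits, and a metabolic trait uncorrelated with those shows no bias. Carry-over depends on a correlation the article does not give.
- **DIABLO.** A reader might also infer that its gain over the breath markers is inflated. The calculation points the other way: an over-fitted baseline leaves less room for improvement.

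The study is a pilot, the step is framed as exploratory, and the Discussion calls for confirmation in a second study. That limits the consequences.

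**Conclusion.** The concern holds for the clinical-trait links. As written, features chosen on a trait are linked to that trait with no stated separation, and a score correlation near 0.83 would be expected from noise alone (0.59 to 0.84 over the settings tried in the modelling set). Such links are uninformative as evidence.

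For metabolic traits the bias is partial. It exists only where a trait overlaps or correlates with a selecting trait. Its size (about 90% false links for a combined score, about 19% per feature) rests on the assumed correlation of 0.5. Canonical correlation forms combinations, so the score figure is relevant, but it is the worse case.

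The DIABLO comparison is distorted by the over-fitted baseline, with the gain masked in the simplified check. DIABLO itself was not simulated.

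The figures depend on the assumed feature count, number selected and univariate ranking. The direction of the clinical-trait result did not change over the ranges tried. The primary result is not affected, and the change is advisable rather than critical.

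**What to change.** In Statistical analysis, Secondary endpoints:

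1. Run the regularised canonical correlation on all quality-filtered breath features, before any selection on traits; or estimate the links from out-of-fold profile scores or in the 20 held-out participants. Held-out estimates will be imprecise: chance alone gives mean |r| of 0.18 to 0.19 at n = 20.
2. Take reference distributions from permutations that repeat the feature selection.
3. If neither is done, report links between profile features and their own selecting traits as descriptive only.
4. Judge any DIABLO gain over the Lactobreath markers out-of-fold.
5. State which participants enter each step, and note that an analysis restricted to selected features has used the trait labels.

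No new data are needed. The cost is wording, more computing time and smaller reported correlations.

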### Missing data and drop-outs

Missing data will be managed by multiple imputations using the moving average method for the intervention postprandial measurements. Missing data for the baseline measures will be handled by imputing the mean of all baseline measurements available for the participant. Additional subjects will be recruited from the group of participants who complete the home survey, should the number of participants completing the lactose and glucose tests fall below the targeted numbers due to drop-outs.

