### Sample collection

During the baseline period, all participants will collect and send by post stool samples for genomic characterisation of the gut microbiota. Faecal samples will be stored at −80°C. They will be analysed using shallow shotgun sequencing for a mechanistic understanding of the microbial features associated with lactose metabolism.

Breath and urine will be sampled on the intervention day, both before and during the 6 hours following the consumption of the assigned test drink. Breath sampling will be performed using a secondary electrospray ionisation source coupled to a high-resolution mass spectrometry system for direct and real-time detection of VOCs and using an H_2_ breath solid-state sensor for detection of exhaled hydrogen. Standardised breath sampling protocols will be developed for precise measurements of biomarkers of dietary intake and metabolism.

In addition, exhaled breath condensate (EBC) samples will be collected using a glass cold trap cooled to −78°C using a mixture of isopropanol. To collect EBC samples, participants exhale through the spirometry filter and a short-length tube, and their exhaled breath condenses in the cold trap. Blank samples will also be obtained by flushing 2 mL of water through the tubing and freezing it in the cold trap. All EBC samples will be stored at −80°C at the premises of ETHZ until thawed for subsequent analysis. Participants will be provided with the needed breath delivery equipment (ie, mouthpiece) and asked to breathe normally for up to twelve times per sample (this includes baseline measurements). Breath samples will be collected before the intervention and at nine time points following the intervention (15 min, 30 min, 60 min, 90 min, 120 min, 180 min, 240 min, 300 min and 360 min). Participants will be asked to provide four urine samples (two baseline samples before the intervention and two sample pools collected during the intervention (0–180 min and 180–360 min). Samples will be stored at 4°C during the test and before further analysis, all urine samples will be stored at −80°C at ETHZ.

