### Analysis of samples

#### Real-time breath measurements (breath metabolome)

On-line chemical analysis of exhaled breath will be carried out by ETHZ using a SESI source purchased from Fossil Ion Technology SL, coupled with an HR-MS system (Q Exactive Orbitrap, ThermoFisher Scientific). SESI-MS is a well-established and robust analytical technology specially developed for in-depth breath characterisation. Its applicability has already been demonstrated in clinical studies previously published by ETHZ.^70^,^77^ The real-time approach of this method is practical for the high sampling frequency planned for the study and has already been shown to be sensitive to acute dietary intervention.^78^

By conducting breath analysis during the 6 hours following the intervention, it will be possible to follow multiple features over time and to obtain a major part of the postprandial kinetic profile of the participants. During a real-time breath measurement using SESI-MS, the participant exhales through a disposable antibacterial mouthpiece and a short-length heated sample transfer line into the ionisation chamber. In the SESI chamber, a mist of charged droplets interacts with breath molecules for charge transfer and ionisation. The produced charged breath molecules are then introduced into the mass analyser for mass-to-charge (m/z) separation and detection. Measurements are carried out in the positive and negative ion mode that facilitates the determination of protonated and deprotonated species, respectively. Exhaled CO_2_, pressure, flow rate and breath volume are simultaneously recorded using an interface (EXHALION) connected at the front-end part of the sample transfer line. Mass calibration and tuning of the system in both ionisation modes are performed once per week or more often if required. The stability of the whole system is monitored daily by introducing gaseous standards (eg, acetone) at known concentrations using a gas standard generation system that additionally allows quantification calculations of target metabolites.

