### Hydrogen breath test

Exhaled breath H_2_ will be measured using a non-invasive hydrogen gas microanalyser (QuinTron BreathTracker Digital Microlyzer, model SC; QuinTron Instrument Company, Milwaukee, Wisconsin, USA). The BreathTracker has a resolution of 1 ppm H_2_ and a linear detection range between 2 and 150 ppm H_2_ with an accuracy of ±2%. It also features a two-step calibration and a purging mode that eliminates cross-interference (inter-subject contamination) and provides a stable internal baseline. The gas analyser will also be calibrated externally using a known-concentration H_2_ compressed gas standard. Breath samples (30 mL each) will be insufflated in the Breath Tracker and will be collected as CO_2_-corrected H_2_, expressed in parts per million (ppm). The maximum increase in breath H_2_ will be calculated by subtracting baseline H_2_ values from the highest H_2_ value post-lactose ingestion based on the BreathTracker readings. An increase of at least 20 ppm hydrogen between any two time points after 30 min in the study will indicate LM.^80 87^

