The diagnostic performance of the lactose-induced breath profiles identified for the clinical traits will be assessed using the following parameters: sensitivity, specificity, positive predictive value, negative predictive value, the likelihood ratio of a positive test, likelihood ratio of a negative test as described by Beyerlein *et al*^17^ and Jellema *et al*.^81^ For each parameter, the novel breath profiles will be compared with the reference diagnostic tool. The participants are grouped by LHBT and genetic test results as these are commonly used in clinical practice for LI diagnosis and are, therefore, suitable for evaluating the performance of the breath biomarkers. The level of significance will be two-sided (α=0.05). Corrections for multiple testing will be made using the false discovery rate.^101^

Analysis populations: the analysis populations are defined by the criteria used to select the three study groups and the two assigned carbohydrate interventions, resulting in six groups for analysis.

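### The missing-data rule names multiple imputation by a moving average, which is one deterministic fill: it carries no imputation uncertainty and records undetermined test-day hydrogen or symptom traits as definite

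*Protocol article*

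**What the plan says.** The section on missing data and drop-outs gives one rule for the test-day series: "Missing data will be managed by multiple imputations using the moving average method for the intervention postprandial measurements". It draws no distinction between breath features, breath hydrogen, symptom scores and urine. The article mentions no random draw, imputation model, number of imputed data sets or pooling rule. Baseline gaps have a separate rule: "Missing data for the baseline measures will be handled by imputing the mean of all baseline measurements available for the participant". Drop-outs are to be replaced by further recruits.

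Three other places matter.

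- Sample collection sets nine post-dose breath samples at uneven spacing: "15 min, 30 min, 60 min, 90 min, 120 min, 180 min, 240 min, 300 min and 360 min".
- The hydrogen breath test section builds its trait on extremes. "The maximum increase in breath H_2_ will be calculated by subtracting baseline H_2_ values from the highest H_2_ value post-lactose ingestion", and "An increase of at least 20 ppm hydrogen between any two time points after 30 min in the study will indicate LM".
- The analysis of the primary endpoint models the hydrogen test response and the GI symptoms as traits to be discriminated, and it compares the breath profiles with the reference diagnostic tool. Tests are two-sided at 0.05 with false discovery rate control.

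**The concern.** Multiple imputation draws each missing value several times from a distribution, analyses each completed data set and adds the variation between sets to the variance. A moving average does none of this. Whoever follows the sentence must either compute a single fill and report it as multiple imputation, or run a real multiple imputation and depart from the stated method.

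The label matters because of what is filled. Test-day hydrogen and symptoms are the traits against which the breath profiles are judged. If a sample near the peak is lost and the remaining samples do not reach the threshold, the trait cannot be determined. Under the rule as written, it becomes a definite negative. Sensitivity, specificity and the predictive values are then computed against a label that nobody observed. The real-time breath section also relies on the shape of the curve ("it will be possible to follow multiple features over time and to obtain a major part of the postprandial kinetic profile of the participants"), so filled values near a peak enter the models as if they had been measured.

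**Working it through.** The plan gives no figure to reproduce. The check has three steps: one of logic and two illustrations on the protocol's sampling times. Curve shapes and missing rates are assumptions, because the article gives neither.

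**1. Variance.** With *m* imputed data sets, within-set variance *W* and between-set variance *B*, Rubin's total variance is T = W + (1 + 1/m)·B. A moving average is a fixed weighted mean of observed neighbours, so all *m* fills are identical, B = 0 and T = W. Twenty repeated fills of one gap gave a variance of about 10⁻²⁹, which is rounding error.

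**2. A lost peak sample.** A mean with non-negative weights lies between the smallest and the largest of its inputs. It can therefore neither restore a lost peak nor create a rise that the observed samples lack. Assume a bell-shaped curve with a true rise of 30 ppm at 180 min and the 180 min sample missing. The neighbours at 120 and 240 min are both 60 min away, so each shows a rise of 30·exp(−0.5·(60/SD)²), and so does their mean.

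| Curve SD (assumed) | Calculation | Filled rise | Against 20 ppm |
|---|---|---|---|
| 45 min | 30 × 0.411 | 12.3 ppm | below |
| 60 min | 30 × 0.607 | 18.2 ppm | below |
| 90 min | 30 × 0.801 | 24.0 ppm | above |

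Wider windows give lower fills. At SD 60 min, two neighbours on each side give 12.5 ppm, and exponential weights give 14.4 ppm (two on each side) or 12.3 ppm (four on each side). The retained maximum is still 18.2 ppm, because the neighbours were observed. A 60 ppm peak stays above 20 ppm in every scenario tried; the lowest retained rise is 24.7 ppm.

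The table uses the rise over baseline. The threshold is worded as a rise between two time points after 30 min. At SD 60 min the 60 min value is 30·exp(−2) = 4.1 ppm above baseline, so the rise is 30.0 − 4.1 = 25.9 ppm with the peak sample and 18.2 − 4.1 = 14.1 ppm without it. The example changes class in the same way.

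**3. A level at one time point.** Assume 60 participants (group 3 on lactose, 72 − 12), individual peaks centred on 180 min (SD 30 min), amplitude 30 ppm (SD 10), curve SD 60 min, measurement noise SD 3 ppm, and 180 min values missing completely at random and filled by the mean of the 120 and 240 min values.

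| Missing at 180 min | Bias of the mean | Reported SE | Bias / SE |
|---|---|---|---|
| 0% | 0 | 1.32 | 0 |
| 10% | −0.9 ppm | 1.32 | 0.7 |
| 20% | −1.8 ppm | 1.32 | 1.4 |
| 30% | −2.7 ppm | 1.30 | 2.1 |

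The reported standard error does not grow as data are lost. The actual spread of the estimates across replicates was also about 1.3 throughout. In this illustration the fault is thus a bias that the interval does not show, and not a standard error that is visibly too small.

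**The case against.** The other side has a strong case on size, and most of it stands.

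- **The loss of the maximum does not come from the moving average.** A reader might infer that this method in particular flattens peaks and turns positive hydrogen tests negative. On assumed curves (peak at 90–240 min, amplitude 20–60 ppm, SD 35–70 min) with the peak sample removed, the maximum rise falls by about 23%, and about 20% of true rises of 20 ppm or more drop below the threshold. The same figures result from time-weighted interpolation and from leaving the gap empty. The filled peak value is 38.0% too low with the moving average and 37.3% too low with interpolation. The lost sample causes this, so these figures cannot be charged to the method.
- **Those figures assume that the peak sample is the one missing.** With 10% of samples missing at random, the same curves give about 2% changed labels. Sampling is done on site and drop-outs are replaced, so the rate may be low.
- **Understated standard errors hardly reach the primary analysis.** It rests on classifiers assessed in 20 held-out participants. Rubin's variance does not enter there. Any inflation factor would need a fraction of missing information that nothing in the article supports.
- **Window, weights and edge rule may be in a fuller plan.** That is so. Faults that depend on an unweighted, one-neighbour window are not established.
- **The three study groups are safe.** They come from genotype and the home test, which this rule does not touch.
- **Multiple may loosely mean that several values are filled.** Then the method is single imputation and should be called that.

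None of this repairs the sentence. A fuller plan can add detail, but it cannot make a moving average into multiple imputation, and an undetermined trait is still recorded as definite.

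**Conclusion.** The point holds in a limited form. The method contradicts itself as stated: a deterministic fill is named as multiple imputation, and no imputation uncertainty can result from it. For test-day hydrogen and symptom traits, a lost sample that could have decided the trait leaves a definite label where the honest answer is unknown. That conclusion follows from the text and from the bounds on a weighted mean, and needs no assumed curve.

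The practical size is not known. It depends on how often samples are lost and on whether they fall near the peak. Rises well above 20 ppm are little affected, and with few gaps the effect on the results may be small. The ppm figures above rest on assumed bell-shaped curves and serve only as illustration. The point does not undermine the design, but the sentence should be corrected before the data are analysed.

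**What to change.** Replace the sentence on postprandial gaps with three rules.

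1. **Breath features.** Isolated interior gaps are filled by time-weighted interpolation within the participant, and this is called single imputation. The final time point (360 min) is not filled. This makes the label honest and respects the uneven spacing; it does not recover a lost peak.
2. **Test-day hydrogen and symptom traits.** Either use real multiple imputation (a stochastic model with time, stratum and arm, a stated number of data sets, pooled by Rubin's rules), or set the trait to missing when a lost sample could change it. A threshold trait that the observed samples already meet stays positive, so only traits that are not met and have a relevant gap are affected.
3. **Model validation.** Any model-based imputation is fitted in the training data only, so that the 20 held-out participants do not inform it.

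The report should give the number of missing samples by time point and measurement, so that readers can judge the effect. The cost is wording, a little programming, slightly wider intervals and possibly a few missing labels.
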